**Methods and design:**

The TULP trial is a prospective, two arm, double blind, randomized controlled trial to assess chronic postoperative pain and quality of life following implantation of a lightweight (Ultrapro) and heavyweight (Prolene) mesh in endoscopic TEP hernia repair. The setting is a high-volume single center hospital, specializing in TEP hernia repair. All patients are operated on by one of four surgeons. Adult male patients (≥18 years of age) with primary, reducible, unilateral inguinal hernias and no contraindications for TEP repair are eligible for inclusion in the study. The primary outcome is substantial chronic postoperative pain, defined as moderate to severe pain persisting ≥ 3 months postoperatively (Numerical Rating Scale, NRS 4–10). Secondary endpoints are the individual development of pain until three years after the TEP procedure, the quality of life (QoL), recurrence rate, patient satisfaction and complications.

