### Follow-up

Several questionnaires are used for the assessment of pain and quality of life (also to evaluate which questionnaire can best be used to evaluate pain and its effect on quality of life in this patient population).

1) To assess the presence of postoperative pain, the following validated questionnaires are used:

Inguinal Pain Questionnaire (IPQ, Dutch version) [18]

Brief Pain Inventory, Short Form (BP-SF, Dutch version) [19,20]

Carolinas Comfort Scale (CCS, Dutch version) [21]

Numerical Rating Scale (NRS, 0 = no pain, 10 = extremely painful, Dutch version)

2) To measure the health related Quality of Life (QoL) the following validated questionnaires are used:

Short Form (36) Health Survey (SF-36, Dutch version) [22]

EuroQol 5D (EQ-5D, Dutch version) [23]

3) Finally, to assess the presence of pain related to sexual function, the PSF (pain related to sexual function) questionnaire is used, which is a Dutch translation of the questionnaire similar to the one previously described by Aasvang *et al.*[24] and based on the International Index of Erectile Function (IIEF) [25] to assess the presence, frequency, intensity and location of pain during sexual activity and the effect of pain on sexual function.

The patient is requested to record – on a daily basis during the first week immediately following surgery – the pain experienced, as well as the type and amount of analgesics used.

The NRS is used to assess the amount of experienced pain, where 0 = no pain and 10 = extremely painful. BPI and SF-36 questionnaires are filled in at Day 1 and Day 7 following surgery, to determine the effect of pain on daily activities.

After 6 weeks and 3, 12, 24 and 36 months, the IPQ, BPI, CCS, NRS, PSF, SF-36 and EQ-5D questionnaires are completed by the patients. To prevent bias, the questionnaires will be completed at home, or at the visit to the outpatient clinic at three months and one year postoperatively, in the absence of the surgeon or coordinating investigator, before the clinical assessment at the outpatient clinic. Patient satisfaction with the operative procedure is assessed at one week and three months after surgery on a 0 (= very unsatisfactory) to 10 (= very satisfactory) Likert scale.

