### End-points

The primary endpoint is the presence of moderate to severe chronic pain three months after an endoscopic preperitoneal (TEP) hernia correction, as measured by the NRS. The definition of the International Association for the Study of PAIN (IASP) is used with chronic postoperative pain being defined as pain still present at the site of the operation three months after the primary surgery and different from the pain before the operation. Pain is measured on a 0 (= no pain) to 10 (extremely painful) scale. In accordance with the literature, the following cut-off values for pain are used: [26]

Mild pain: NRS 1 to 3

Moderate pain: NRS 4 to 6

Severe pain: NRS 7 to 10

Moderate to severe pain is considered as clinically relevant [26]. Only moderate to severe pain (NRS 4 to 10) will, therefore, represent ‘chronic pain’ in this study. Secondary endpoints are:

Duration of hospital stay

Complications: intra-operative, post-operative period (until three months after surgery), long-term (until three years after surgery, for example, testicular atrophy)

Time to resume daily activities and return to work

Recurrent hernia

Contra-lateral hernia

Development of pain over time as measured by the NRS score at the first week following TEP repair and 6 weeks, 12, 24 and 36 months postoperatively

Development of pain over time as measured by the BPI, IPQ and CCS questionnaires: the presence of pain in the first week postoperatively and after 6 weeks, 3 months, 12, 24 and 36 months

Development of pain, sensitivity disorders (anesthesia, hypoesthesia, hyperesthesia, allodynia) and or discomfort (including sensation of ‘mesh presence’ at the outpatient visit at three months and one year post-operatively

Health related quality of life as measured by the SF-36 and EQ-5D questionnaires

Pain related sexual function as measured by the PSF questionnaire

Patient satisfaction with the procedure and perioperative care

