### Statistical methods

Data will be analyzed according to the intention-to-treat principle. SPSS software (SPSS, Chicago, IL, USA) will be used for statistical analysis. Descriptive statistics are used for baseline data. The incidence of the primary endpoint (moderate to severe chronic pain three months after endoscopic TEP repair as based on a NRS 4 to 10) will be compared between the Ultrapro and Prolene mesh group by means of Chi-square analysis. The comparisons of pain will be adjusted for analgesics used as a secondary supporting analysis. The number-needed-to-treat to prevent one case of chronic pain will be calculated. In an additional multiple logistic regression model, the effect of treatment on the primary endpoint will be assessed in relation to important risk factors for pain (younger age, severe pain in the postoperative period and severe preoperative pain [27]). Secondary endpoints will be analyzed by using a Student’s *t*-test (normally distributed continuous), Mann–Whitney analysis (not normally distributed continuous) or Chi-square analysis (categorical variables). The individual development of pain over time will be analyzed with repeated measurement strategies. Effect estimators are described with 95 % confidence intervals. Significance is set at a level of *p ≤ 0.05*.

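### Quality-of-life scores collected at five to seven postoperative times are left to two-sample tests; extending the repeated-measures method planned for pain, with the preoperative score as covariate, would be a cheap improvement

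*Protocol article*

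**What the plan says.** Under Statistical methods, the protocol article sorts secondary endpoints by type and distribution. Continuous ones get a Student's t-test or a Mann–Whitney test, and categorical ones a chi-square test: "normally distributed continuous), Mann–Whitney analysis (not normally distributed continuous) or Chi-square analysis (categorical variables". The next sentence is the only one that names a longitudinal method, and it concerns pain: "The individual development of pain over time will be analyzed with repeated measurement strategies". A general sentence then covers reporting: "Effect estimators are described with 95 % confidence intervals".

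The secondary endpoints (End-points) include "Health related quality of life as measured by the SF-36 and EQ-5D questionnaires" and "Pain related sexual function as measured by the PSF questionnaire", with no time point attached to either. Under Follow-up, the SF-36 is completed at Day 1 and Day 7. At 6 weeks and 3, 12, 24 and 36 months, "the IPQ, BPI, CCS, NRS, PSF, SF-36 and EQ-5D questionnaires are completed by the patients". Table 2 shows that the SF-36, EQ-5D and PSF are also collected before surgery.

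The Abstract makes quality of life part of the trial's purpose: "to assess chronic postoperative pain and quality of life". The Discussion names the return of questionnaires as a main challenge. It plans face-to-face contact at three months and one year and telephone reminders.

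**The concern.** The analysis named for quality of life uses less of the data than the design collects. A two-sample test takes one value per man. Whichever visit or summary it is applied to, it makes no use of the preoperative score, and a test at one visit makes no use of the others. Without imputation, a man who skipped the 36-month form contributes nothing to the 36-month comparison, even if he returned every earlier form. The 24- and 36-month scores are the most exposed, because the planned outpatient visits are at three months and one year.

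At stake is the precision of a named aim of the trial and, to a smaller degree, its protection against selective non-return. The article already plans repeated-measures methods for pain collected on much the same schedule, so quality of life is treated less well for no stated reason.

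**Working it through.** **Plan's own figure.** The article states no sample size or effect for quality of life. Its only calculation is for the primary endpoint: 23% against 15.5% (23% minus 7.5 points), two-sided alpha 0.05, power 0.80. The unpooled formula gives

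n = (1.960 + 0.842)² × (0.23 × 0.77 + 0.155 × 0.845) / 0.075² = 7.849 × 0.3081 / 0.005625 = 429.9,

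so 430 per arm (433 with the pooled variance), against 429 stated. For 10% loss, 858 / 0.90 = 953.3, so 954 against 950 stated. The plan's figures are reproduced closely, and 429 per arm is used below.

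**Visits (Follow-up, Table 2).** SF-36: Day 1, Day 7, 6 weeks, 3, 12, 24 and 36 months, which is 7. EQ-5D and PSF: the last 5. All three also have a preoperative value.

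**Detectable difference at 80% power.** Assumed: 429 per arm with complete data, equal SD at all times, and one correlation ρ between any two times, baseline included. The article gives no correlation, so ρ runs from 0.3 to 0.7. The detectable difference in SD units is 2.802 × √(2v/429), with variance factor v:

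| Analysis | v | ρ = 0.3 | ρ = 0.5 | ρ = 0.7 |
|---|---|---|---|---|
| One visit, t-test | 1 | 0.191 | 0.191 | 0.191 |
| One visit, baseline-adjusted | 1 − ρ² | 0.182 | 0.166 | 0.137 |
| Mean of 5 visits | (1 + 4ρ)/5 | 0.127 | 0.148 | 0.167 |
| Mean of 5 visits, baseline-adjusted | (1 + 4ρ)/5 − ρ² | 0.113 | 0.113 | 0.099 |

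For a true difference of 0.15 SD, power is 59% with the single-visit t-test and 96%, 96% and 99% with the baseline-adjusted five-visit mean.

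**One late visit, no baseline.** A fraction m of forms is missing at that visit. With one earlier visit available, the variance ratio of the likelihood analysis to the responders-only analysis is 1 − mρ². For ρ = 0.5 to 0.7 this gives 0.975 to 0.951 at m = 0.10 and 0.950 to 0.902 at m = 0.20, so variance is about 2.5–10% lower. With four complete earlier visits and ρ = 0.3 to 0.7, the standard error is 1–3% lower at 10% missing and 3–10% lower at 30% missing. The gain is small either way.

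**Selective return.** Assumed: early pain lowers a late 0–100 score by 25 points, and return is 90% against 70% according to early pain.
- True difference: (0.23 − 0.155) × 25 = 1.88.
- If men with early pain return more often, their share among responders is 0.2775 against 0.1908, and 0.0867 × 25 = 2.17.
- If they return less often, the shares are 0.1885 and 0.1249, and 0.0637 × 25 = 1.59.

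The error is about 0.3 point in either direction.

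**t-test or Mann–Whitney.** Assumed: 427 per arm; scores 0–100 in steps of 5; mean 60, SD 20 for men in pain and mean 87.5, SD 13 for the others. If the mesh changes only the share in pain (23% against 15.5%), simulated power is 0.41 for the mean difference and 0.31 for Mann–Whitney. If it shifts all scores, the order reverses: 0.31 against 0.39 for 2 points, and 0.81 against 0.91 for 4 points.

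**The case against.** The strongest reply is that the planned tests are valid, that these are secondary endpoints, and that the article condenses a fuller protocol. It does not say that the tests are run at every visit, and it neither describes nor excludes imputation. That stands: the loss of non-returners' data is conditional on there being no imputation, and the missing detail is not itself a fault. What remains is a method that the text does state, alongside a better one that it states for pain only.

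A reader might go further in four ways that the article does not support.

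- **That quality of life gets no effect estimate.** The promise of estimators with 95% confidence intervals is not limited to any endpoint. At most, the estimator to accompany a Mann–Whitney test is not named.
- **That much of the hypothesised contrast would be missed.** The stated hypothesis concerns the incidence of chronic pain. That is the primary endpoint, tested by chi-square and untouched here.
- **That choosing the test by distribution should be abolished because it costs power.** Which test has more power depends on the form of the effect, as the simulation shows, and the article states no quality-of-life effect of either form.
- **That PSF results are continuous scores misassigned to these tests.** The article describes presence, frequency, intensity and location of pain and gives no summary score, so some items may belong to the chi-square branch.

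It is also fair that the planned reminders and visits should limit non-return, and that the illustrated error from selective return is small: about 0.3 point, against a standard error of about 1.15 points under the score distributions assumed above.

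**Conclusion.** The point holds as an improvement to a secondary analysis, not as an error that invalidates one. As written, the SF-36 and EQ-5D go to tests that leave the preoperative scores and the other visits unused, although the schedule collects both and non-return is expected.

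The gain can be large: 0.19 SD detectable falls to about 0.10–0.11 SD. Most of it comes from adjusting for baseline and averaging visits. The comparison is not like for like, since an average over visits answers a different question from a single-visit contrast. At one visit, baseline adjustment alone gives 0.14–0.18 SD. If the preoperative score proved uninformative, the five-visit mean would still give 0.13–0.17 SD. A mixed model without baseline, read at one late visit, gains little. All of these figures rest on assumed correlations and a simple covariance pattern. The primary analysis and the sample size do not change.

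**What to change.** For each SF-36 scale and EQ-5D score, and for any set of PSF items that yields a continuous score, specify a linear mixed model over all postoperative visits. It should contain mesh, visit, mesh-by-visit and the preoperative score as covariate, with unstructured covariance and every returned form. Report the mean difference with 95% CI at each visit and averaged over the later visits (6 weeks to 36 months). State how a man without a preoperative form is kept in the model. The existing rule can stay for the other secondary endpoints.

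The cost is a few sentences of analysis text and a little more programming, for example SPSS MIXED, with no new data. The downside is that the model assumes data missing at random given the forms returned, so it does not protect against non-return that depends on the unseen score itself.

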## Discussion

The TULP trial is a prospective, randomized controlled (RCT) clinical trial of a lightweight mesh (Ultrapro) and a heavyweight mesh (Prolene) in endoscopic TEP hernia repair designed to analyze the outcomes regarding chronic postoperative pain and quality of life.

Although a limited number of randomized studies assessing the outcomes after implantation of a lightweight and heavyweight mesh in endoscopic TEP hernia repair has been published previously, the TULP trial is, to our knowledge, the first randomized controlled trial with a large patient population and a long-term follow-up assessing pain as a primary endpoint and the effect of pain on quality of life. The main challenges that we anticipate are the recruitment and follow-up of trial participants, (following the findings of a previous pilot study patients who visit our hernia clinic are ‘busy’ male patients in the ‘prime of their lives’, who do not always ‘feel like it’ to fill in and return questionnaires). We aim to maximize participant follow-up by face-to-face contact (at three months and one year after TEP repair) and telephone contact as a reminder to return the questionnaires.

There are some limitations of this study. Due to the different characteristics of the meshes, blinding of the operating surgeon is not possible. Nevertheless, the investigator-related bias for the (primary) endpoints is expected to be negligible, since both the coordinating investigator as well as the surgeon involved in the follow-up of the patients, are blinded for the type of mesh. In this study, the same investigator will be present during all patient visits at the outpatient clinic in order to improve consistency of the results and reduce the loss-to-follow-up rates.

In addition, the setting of this study is a high volume center, specialized in endoscopic TEP hernia repair. Despite an inclusive set of patients, a criticism might be that the findings may not be easily generalized to other, less experienced, TEP surgeon settings. On the other hand, the TEP technique has a long(er) learning curve. Expertise is, therefore, a prerequisite in performing TEP and most centers deliver TEP in the hands of expert surgeons, which enables extrapolation of the results of this study.

This prospective, double blind, randomized clinical trial is designed to compare the incidence of chronic postoperative pain following the implantation of heavyweight (Prolene) and lightweight (Ultrapro) mesh in endoscopic TEP hernia repair. As the presence of pain in the groin region, quality of life, return to daily activities and work, patient satisfaction, complications and recurrences are assessed in a large cohort of patients with a sufficient long follow-up period, this study will provide a complete efficiency and feasibility assessment of both meshes in endoscopic TEP hernia repair.

### Trial status

This study has been approved by the regional Medical Ethics Committee (VCMO, Nieuwegein, the Netherlands) and the local Ethics Board of the Diakonessenhuis Utrecht, the Netherlands. This study is performed in accordance with the ethical standards of the Declaration of Helsinki. Recruitment of patients started on 12 March 2010. To date (1 July 2011), 569 patients have been included in the study. Depending on the number of patients needed to be included in the trial (see sample size considerations), recruitment of the 950 patients is currently expected to end in June 2012. Analysis and reporting of data are subsequently expected eight months (outcomes three months after TEP repair) and three and one half years (outcomes three years after TEP repair) later to be complete (October 2012 and October 2015 respectively). The TULP study is registered in the Dutch Trial Register (NTR2131).

## Abbreviations

ASA score: American Society of Anesthesiologists score; BMI: body mass index; BPI: Brief Pain Inventory; BP-SF: Brief Pain Inventory, Short Form; CCS: Carolinas Comfort Scale; CONSORT: Consolidated Standards of Reporting Trials; EPD: electronic patient chart; EQ-5D: EuroQoL 5D; IASP: International Association for the Study of PAIN; IIEF: International Index of Erectile Function; IPQ: Inguinal Pain Questionnaire; NRS: numerical rating scale; PSF: Pain-related Sexual Function Questionnaire; QoL: quality of live; RCT: randomized controlled trial; SAE: serious adverse events; SF-36: Short-form 36; TAPP: Transabdominal preperitoneal; TEP: totally extraperitoneal.
